## Abstract

**Background:**

Cannabinoids such as cannabidiol (CBD) exhibit anti-inflammatory properties and have the potential to act as a therapeutic following mild traumatic brain injury. There is limited evidence available on the pharmacological, physiological and psychological effects of escalating CBD dosages in a healthy, male, university athlete population. Furthermore, no dosing regimen for CBD is available with implications of improving physiological function. This study will develop an optimal CBD dose based on the pharmacokinetic data in contact-sport athletes. The physiological and psychological data will be correlated to the pharmacokinetic data to understand the mechanism(s) associated with an escalating CBD dose.

**Methods/design:**

Forty participants will receive escalating doses of CBD ranging from 5 mg CBD/kg/day to 30 mg CBD/kg/day. The CBD dose is escalated every two weeks in increments of 5 mg CBD/kg/day. Participants will provide blood for pharmacological assessments at each of the 10 visits. Participants will complete a physiological assessment at each of the visits, including assessments of cerebral hemodynamics, blood pressure, electrocardiogram, seismocardiogram, transcranial magnetic stimulation, and salivary analysis for genomic sequencing. Finally, participants will complete a psychological assessment consisting of sleep, anxiety, and pain-related questionnaires.

**Discussion:**

This study will develop of an optimal CBD dose based on pharmacological, physiological, and psychological properties for future use during contact sport seasons to understand if CBD can help to reduce the frequency of mild traumatic injuries and enhance recovery.

**Trial registration:**

Clinicaltrials.gov: NCT06204003.

## Background

Plant-based (phyto) cannabinoids such as cannabidiol (CBD) and Δ^9^-tetrahydrocannabinol (Δ^9^-THC) have been generating increasing research interest due to their proposed therapeutic properties. These include pain relief, neurogenesis and reduced inflammation [1, 2]. The short- and long-term effects of brain injury, especially sport-related concussion (SRC), or mild traumatic brain injury (mTBI), pose serious challenges for our health care system. Currently, there are gaps in the literature related to the medical benefits of using CBD for this clinical population. Key gaps include information regarding safety of daily consumption, optimal dosage for physiological function, possible neuroprotective effects, and whether they can be used to reduce prescription medications, including opioids, for chronic pain management [3].

While there is a theoretical framework for CBD use for brain injury, the evidence is currently limited [4–8]. Sport-related concussions appear to induce stress on the entire body, with alterations in heart function, immune responses, and cerebral hemodynamic activity [9–12]. Specifically, impairments in heart rate variability, baroreflex sensitivity, blood pressure variability, cerebral blood flow velocity, and cerebral oxygenation can occur during acute concussion and in those with a history of concussions [13–19]. Therapeutic options are currently limited, and recently, there has been interest in treating brain injuries with cannabinoids such as CBD, with an emphasis on concussion [4]. Recognition that the endocannabinoid system (eCB) system regulates neurotransmission and inflammatory processes in part through the type 1 and 2 cannabinoid receptors (CB1 and CB2) [8, 20], prompted investigations into how phytocannabinoids could be used to modulate neurotransmitter release and inflammation [21], ultimately leading to neuroprotection [22, 23]. As such, understanding how different CBD doses influence physiological and pharmacological parameters will allow us to provide an optimal dose for future research to administer in a competitive sports season for enhanced neuroprotection.

CBD appears to work via a number of receptors, including non-cannabinoid receptors, such as the G-protein-coupled receptors serotonin 1A and adenosine A2a, the ligand-gated vanilloid receptor ion channels, and the nuclear peroxisome proliferator-activated receptors [4, 24]. Collectively, modulation of these receptors can result in extensive anti-oxidative and anti-inflammatory effects, along with influencing hemodynamic activity [4, 25, 26]. Consequently, CBD has the potential to limit blood brain barrier permeability, improve cerebral functional connectivity, and the heart-brain axis interactions following mTBI [4, 24]. To date, no research has examined CBD-mediated neuroprotection in elite contact sport athletes, but such effects have been inferred [3, 4, 27]. Furthermore, specific dosage, pharmacokinetic, and pharmacodynamic data are lacking, or are difficult to compare between studies that use different sources of CBD [28].

This protocol presents the first of a three-part research project aimed at investigating the pharmacological, physiological, and psychological effects of CBD in healthy, young (18–35 years) males. Female participants are excluded as the study needs to be directly applicable to the National Football League (NFL) players due to the funding requirements, requiring our sample to be male. We also predominantly recruited participants that played American style Football. However, our future research will include a similar study in female participants participating in contact sports. The primary objectives and endpoints are to develop an optimal CBD dose based on the pharmacokinetic data in contact-sport athletes. The secondary objectives include direct neurophysiological and pharmacological analyses to understand the mechanism(s) associated with the primary objective findings. The primary research hypothesis is that CBD formulations are non-intoxicating (non-psychotropic), safe, well-tolerated and do not cause adverse physiological or psychological dysfunction. Specifically, a placebo-washout, dose escalation Phase I clinical trial will be conducted to document the effects of increasing dosages of CBD on pharmacokinetic and pharmacodynamic parameters to determine what is an ‘optimal’ formulation for daily administration for physiological function. This dose will be applied to future research studies to understand the influence of CBD on neuroprotection from concussion. The secondary hypotheses are:

Plasma levels of CBD and/or its active metabolites will correlate with cerebrovascular, neurophysiology and cardiovascular physiology outcome variables.Saliva levels of CBD and/or its active metabolites will correlate with plasma samples.

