## Methods and design

### Study design

We will complete a two-centre, phase 1, open-label dose escalation study to determine the safety and tolerability of CBD in healthy male athletes. The study will be conducted in two centres in Canada (Regina and Saskatoon, SK). The study consists of a baseline phase, a treatment phase, and a post-dosing phase. Figure 1 illustrates the study visits.

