### Withdrawal criteria

Study participants may withdraw from the study at any point. Participants will be withdrawn if they suffer from any intolerable adverse effects resulting from the CBD intervention, if they fail to attend required site visits, or they are noncompliant with the CBD dosing regimen. For transparency, though, all participants withdrawn from the study will be included in the final report.

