### Sample size justification and statistics

Due to the limited research available, we will assume a 0.5 correlation between 10 successive data time points. To detect a 0.25 moderate effect size in cardiovascular metrics (blood pressure and heart rate variability) with 90% power and 95% confidence, 36 total participants are required. To account for dropout and non-compliance rates, 15–20% more participants will be recruited in each study. Statistical analysis will be performed using IBM® SPSS® Advanced Statistics, and a combination of statistical analyses will be used depending on the outcome variable. In general, multiple repeated multilevel linear mixed models will be used with statistical significance set at p ≤ 0.05.

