While the study presents with fundamental strengths for assessing changes in physiological, neurophysiological and pharmacological activity, there are limitations associated with our methods. First, the study is not randomized, meaning there is potential for bias in our physiological results in association with higher CBD dosages. Furthermore, participants and researchers are not blinded to the condition, which can bias some of the outcomes. However, our primary outcome is the PK data, which will not be influenced by participant blinding. We are limited to assessing static and dynamic cerebral autoregulation. As such, we will not have an understanding of how cerebrovascular reactivity and neurovascular coupling are affected by CBD. While our participants are required to be at least 18 years of age, little is known about neurodevelopmental process from chronic CBD administration [61]. Regarding pharmacokinetic activity, we are hypothesizing that 2-weeks is sufficient to reach a steady state of CBD plasma concentrations, although research is currently lacking. Finally, given the large amount of time required per participant, we are unable to assess other aspects of cognitive and physical function, such as perceptual-cognitive and functional motor control assessments.

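### The primary hypothesis is that CBD does no harm, but the only inferential criterion the article states is one for detecting a difference, which can refute that hypothesis and cannot support it

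*Protocol article*

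**What the plan says.** The Background states: "The primary research hypothesis is that CBD formulations are non-intoxicating (non-psychotropic), safe, well-tolerated and do not cause adverse physiological or psychological dysfunction". Study design describes a "phase 1, open-label dose escalation study to determine the safety and tolerability of CBD in healthy male athletes".

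The same Background gives a different primary aim, "The primary objectives and endpoints are to develop an optimal CBD dose based on the pharmacokinetic data in contact-sport athletes", and the Discussion repeats that "our primary outcome is the PK data, which will not be influenced by participant blinding".

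Under Sample size justification and statistics, "we will assume a 0.5 correlation between 10 successive data time points". The target is "To detect a 0.25 moderate effect size in cardiovascular metrics", namely blood pressure and heart rate variability, with 90% power and 95% confidence, and the result is 36 participants. The section then says that, in general, "multiple repeated multilevel linear mixed models will be used with statistical significance set at" p ≤ 0.05. It also allows a mix of analyses according to the outcome variable. The article gives no margin, acceptable event rate or tolerability criterion.

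Withdrawal criteria says: "Participants will be withdrawn if they suffer from any intolerable adverse effects resulting from the CBD intervention". Missed visits and non-compliance with dosing also lead to withdrawal. All withdrawn participants are to appear in the final report. The adverse event sections provide for recording every adverse event.

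**The concern.** The hypothesis asserts that something is absent. The sample size and the significance level are built to show that something is present. If the test is significant, the hypothesis is in doubt. If it is not, the result fits no harm, but it also fits a harm too small or too variable to be seen at this sample size. An analysis plan written to match the statistics section would carry this mismatch forward.

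The withdrawal rule pulls the same way. Everyone climbs the same six levels, so someone withdrawn for intolerance at one level contributes no measurements at the levels above it. The visits at the highest doses then describe a group selected for tolerance.

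At stake is what the trial may say about safety and tolerability, the stated purpose in Study design, before a dose goes forward to studies during a sports season.

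**Working it through.** **Inputs.** From Sample size justification and statistics: correlation ρ = 0.5, 10 time points, effect size 0.25, power 0.90, significance level 0.05, N = 36. From Study population: 40 recruited. Two-sided tests, a true change expressed in SD units and independent events are my assumptions.

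**1. The plan's own figure.** Read 0.25 as Cohen's f for one within-person factor with m = 10 visits and sphericity. The non-centrality is λ = f²·N·m/(1 − ρ), with m − 1 and (N − 1)(m − 1) degrees of freedom.
- N = 17: λ = 0.0625 × 17 × 10/0.5 = 21.25, power 0.904. So 17, not 36, is the smallest N with 90% power.
- N = 36: λ = 45, power 0.9995.

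The stated 36 is not reproduced from the stated inputs. It does appear with three measurements instead of ten (power 0.906). That is a separate matter, and the point below does not depend on it.

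**2. Precision of one change from the placebo visit (Visit 3).** The SD of a within-person change is SD·√(2(1 − ρ)) = SD·√(2 × 0.5) = SD. The 95% half-width is t(0.975, N − 1)·SD/√N.
- N = 36: 2.030/6 = 0.338 SD.
- N = 40: 2.023/6.325 = 0.320 SD.

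An observed change of exactly zero would therefore still be compatible with a shift of about a third of an SD.

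**3. How often a real change is missed (N = 36, one paired comparison, two-sided 5%).**

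| True change | Probability of p > 0.05 |
|---|---|
| 0.25 SD | 69% |
| 0.30 SD | 58% |
| 0.50 SD | 17% |

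**4. The overall test does not settle it.** Its near-complete power in step 1 is for f = 0.25 over ten visits. Suppose instead that harm appears only at the top dose, as a 0.25 SD shift at one visit of ten. Then f = 0.25·√(0.1 × 0.9) = 0.075 and λ = 0.005625 × 36 × 10/0.5 = 4.05. Power is about 22%.

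**5. Adverse events.** With no events in N participants, the exact two-sided 95% upper limit is 1 − 0.025^(1/N).
- N = 40: 8.8%.
- N = 36: 9.7%.

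An event with a true risk of 5% goes entirely unseen in 40 people with probability 0.95^40 = 13%.

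**6. Selection by withdrawal.** The article predicts no rate of intolerance. As an illustration only, take the difference between the 40 recruited and the 36 required, 4 people, and suppose that all four left for intolerance. Over all dosed participants the failure proportion is 4/40 = 10% (exact 95% interval 2.8% to 23.7%). Among the 36 still dosing it is 0/36. The choice of denominator decides which figure describes the top dose.

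**7. Would a formal equivalence test do instead?** The article gives no margin, so margins are assumed, in SDs of the within-person change, with true change zero, two one-sided tests at 5% and a single comparison.

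| Assumed margin | Power at N = 36 | N for 90% power |
|---|---|---|
| 0.25 | 1.6% | 175 |
| 0.30 | 12% | 122 |
| 0.40 | 52% | 70 |
| 0.50 | 81% | 45 |

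At this size, formal equivalence is realistic only for wide margins.

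**The case against.** The strongest reply is that the article never says safety will be decided by the p-value. Mixed models apply only in general, other analyses are allowed by outcome, and safety has its own laboratory tests, symptom rating scale and adverse event recording. The primary outcome is pharmacokinetic, and dose choice is tied mainly to it. Margins, denominators and exact intervals are commonly left to an analysis plan, which is not shown. Selection at higher doses is inherent in escalation within persons.

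Much of this stands, and it rules out three stronger readings that a reader might infer.
- That the analysis is confined to completers: no section says so. Withdrawn participants are to be reported, and a mixed model ordinarily uses all available visits.
- That a non-significant result will be declared safe: no section says so.
- That the dose for later studies rests on a non-significant safety test: the article does not make it so.

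The reply does not remove the mismatch that the article itself fixes: a primary hypothesis of no harm beside a sample size and significance level for detecting change. An unseen analysis plan may add to this, but the stated criterion cannot support the stated hypothesis. Listing withdrawals in the report makes the selection visible. It does not put those people into the estimates at doses they never reached. That pharmacokinetics is the primary outcome adds to the difficulty, because the primary hypothesis then matches neither the primary outcome nor the basis of the sample size.

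**Conclusion.** The concern holds in this form: nothing in the stated inferential criterion could support the primary hypothesis, and at this sample size a non-significant result is not evidence of no harm. The size is about ±0.34 SD for a single change at 36 participants, and an upper limit of 8.8% for an event not seen in 40. Estimates at higher doses come only from people who tolerated lower ones.

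The ±0.34 SD rests on the article's correlation of 0.5, equal variance across visits and one pairwise comparison. For a change of f = 0.25 spread over all ten visits the overall test has ample power, so the weakness concerns single dose levels and event rates. The extent of selection by withdrawal cannot be known in advance; the figure of four is an illustration, not a prediction.

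**What to change.** State the safety and tolerability aim as estimation.
- At each dose level, report the change from Visit 3 with its 95% confidence interval, and say that p > 0.05 will not be taken as evidence of safety.
- Report tolerability per dose level with exact confidence intervals over all dosed participants. Count a withdrawal for intolerance as a failure at that level and every higher one.
- In those who stop dosing, go on collecting adverse event and Visit 10 data where consent allows.
- Limit the claim of non-intoxication to what the listed measures can show. The rating scale covers sleepiness/lethargy, irritability, nausea/vomiting and diarrhea, and no instrument is identified as measuring intoxication.

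Formal equivalence margins are optional, given the low power for small margins at 36.

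The cost is a change of analysis wording, slight extra follow-up of those who stop dosing, and a more cautious safety claim. The sample size need not change.

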## Methods and design

### Study design

We will complete a two-centre, phase 1, open-label dose escalation study to determine the safety and tolerability of CBD in healthy male athletes. The study will be conducted in two centres in Canada (Regina and Saskatoon, SK). The study consists of a baseline phase, a treatment phase, and a post-dosing phase. Figure 1 illustrates the study visits.

**Fig. 1 Fig1:**
[figure not shown]
Overview and Schedule for the Study Protocol. Dosing regimen and assessments to be completed at each visit. Neary protocol derived from [36]

### Study population

We will recruit 40 participants across two study sites. Eligibility to participate in the study include the following criteria:Healthy male adults between 18–35 years of age that compete (in any level, including recreational, collegiate, professional) in contact sport athletics (including American football, soccer, rugby, wrestling, and hockey).Non-smokers without known medical complications.Ability to maintain commitment to all proposed biopsychological and health questionnaires, and neuro-physiological and physiological laboratory tests.

Participants meeting any of the following criteria are excluded from the study:

Currently under treatment (e.g., by a physician or clinical psychologist) for anxiety, depression, post-traumatic stress disorder, mood disorder, psychotic disorders or any cerebrovascular and cardiovascular complications.Unable to maintain commitment to all proposed biopsychological and health questionnaires, and neuro-physiological and physiological laboratory tests.

Since the study is employing a continuous dose escalation design, a placebo-washout design will be implemented. All participants will first intake a placebo for 2 weeks prior to beginning their CBD dosing protocol. As such, no participant randomization of participants will occur, and neither the study participants nor the study investigators will be blinded to the CBD dose. As we will likely recruit the majority of the participants from the university population, they are expected to be in their off-season.

### Intervention

Study participants will receive escalating doses of CBD ranging from 5 mg CBD/kg/day to 30 mg CBD/kg/day. The CBD dose is escalated every two weeks in increments of 5 mg CBD/kg/day. The investigational product is a 99% CBD isolate (GVB Biopharma, OR, USA) using conventional distillation and extraction industry techniques under Good Manufacturing Practices (GMP). The product is regulated by the Access to Cannabis for Medical Purposes Regulations under the supervision of Health Canada's Good Manufacturing Practices. Health Canada requires any cannabis product to be free from molds, mycotoxins, and pesticides and that the concentration of CBD is verified by an independent third-party laboratory.

### Procedures

#### Baseline Phase

##### Visit 1 (Day -15): Consent

Participants who meet the eligibility criteria and have signed the informed consent will be enrolled into the study. From each participant, a medical history (including demographics such as height, body mass), health questionnaires (paper and pen), and a saliva sample will be taken. Participants will receive a logbook to record any side effects associated with the study product during the treatment phase. This session will take approximately 20–30 min to complete. The body mass recorded at this initial visit will be used for the dosing regimen.

Participants will be asked to refrain from taking Cannabis or Hemp products between study Visit 1 and 2 (approximately 2 weeks later) to ensure undetectable cannabinoid levels in their blood at the commencement of the treatment phase. As well, participants will be instructed to not smoke, use chewing tobacco, or use any Cannabis or Hemp products besides the study CBD for the duration of study. These are important requirements to continue in this study. Participants will be asked to not complete Visit 1 and to terminate the study if they feel that they cannot adhere to these requirements.

##### Visit 2 (Day 0): Baseline Tests

Participants will provide blood (to confirm that participants do not have measurable cannabis products in their bloodstream) and saliva samples, complete the biopsychological and health questionnaires, and perform the neuro-physiological and physiological laboratory tests. This entire session will take approximately 2–3 h.

At the end of Visit 2, participants will be given a 16-day supply of study Placebo to be taken orally over the next 2-weeks. The Placebo (cornstarch maltodextrin powder) will be supplied as appropriately labelled, individual dosing units (glass vials), and participants will be provided with a hand-out that explains the administration of the placebo. A small amount of extra Placebo will be provided to allow for some flexibility in scheduling the next appointment. Participants will be instructed to take an individual dosing unit twice per day, once in the morning at breakfast and once at prior to sleeping at night, with an aim for each dose to be 12 h apart. The study placebo will be taken with 250 mL of water and a Blender Bites smoothie ‘puck’ and given to participants by one of the researchers conducting the study. Further, the participants will be asked to record any adverse effects into the Logbook provided to them on Visit 1.

##### Treatment Phase

Visit 3–9 (Days 15—97).

At Visit 3 (Day 15) participants undergo the same laboratory testing procedures as conducted during the baseline assessments. They will be told to discontinue the Placebo product and will receive the CBD from a study researcher. The CBD product will be supplied as appropriately labelled, individual dosing units (glass vials) and participants will be provided with a hand-out that explains the administration of the CBD product. The first CBD dose at that particular dosing level will be administered to the participant. Participants will be instructed to take an individual dosing unit twice per day, once in the morning at breakfast and once in the evening approximately 10 – 12 h since the morning dose. The study drug will be taken with 250 mL of water and a Blender Bites smoothie ‘puck’ (https://blenderbites.com/). Further, the participants will be asked to record any adverse effects into the Logbook provided to them on Visit 1.

After 2 weeks of treatment, participants will return to the study laboratory for follow-up testing that includes blood and saliva sampling, biopsychological and health questionnaires, and neuro-physiological and physiological laboratory tests. They will return all empty and unused individual dosing units to allow the study research personnel to determine compliance. They will be told to discontinue the current CBD dosing level and will receive a supply of higher dose CBD product according to the dose escalation schedule. Blood samples will be taken prior to the next CBD dose level administration to allow determination of plasma concentrations of CBD and its metabolites prior to increasing the dose. Immediately following the blood sampling, the participant will be administered the new CBD dose level. Participants will be asked to update the researchers regarding any symptoms or adverse events, and to record these in their Logbook. Visit 9 represents the end of the treatment phase. Participants will discontinue the CBD product and will return all empty and unused samples to the study researchers.

